## Abstract

**Background:**

Individuals with spinal cord injuries (SCI) are prone to pressure ulcers (PUs) because of the loss of sensorimotor function involved as well as increased skin moisture. Treatment of PU after SCI is complicated, involving different specialties and with need for long-lasting follow-up. This study should identify risk factors for PU after SCI, and find an effective and less time-consuming treatment for the condition among different available methods for follow-up.

**Method/design:**

The first part of this research project aims to investigate the prevalence of PU among persons with SCI based on an epidemiological design. The study will identify possible risk factors for acquiring PU. A questionnaire focusing on previous and present PUs will be sent to persons who suffered SCIs between January 2004 and January 2014. In the second part we will compare two different treatment regimens of PU through a randomized controlled pilot trial (RCT) where we will compare outpatient SCI follow-up in a hospital versus outpatient follow-up from the patient’s home, using telemedicine (teleSCI) interventions. We will compare the healing of the PU in the two groups (usual care versus teleSCI). The Tissue, Infection, Moisture Edge (TIME) registration form, the Photographic Wound Assessment Tool (PWAT) and the change in the ulcer size will be used to monitor the healing. Changes in health-related quality of life (HRQoL) and the need for assistance will be assessed using the Five Dimensions European Quality of Life scale (EQ-5D), the generic Medical Outcomes Study 12-item Short Form Health Survey (SF-12) modified version, the International Spinal Cord Injury Quality of Life Data set (ISCI-QoL Data set), and the Spinal Cord Independence Measure scale, version III (SCIM III). In addition to primary outcome measures, a cost-benefit evaluation and an assessment of patient satisfaction and participation will be performed, using customized questionnaires.

**Discussion:**

The first part of the research project will reveal the epidemiology of PU after SCI, and explore the risk factors. This part enables further prevention of PU after SCI and this information will be used in the follow-up RCT. Videoconferencing in the outpatient follow-up of persons with SCI and PU will change clinical routines and facilitate interdisciplinary collaboration, communication and competence exchange among participants of the health care services. Our research protocol allows comparing methods for interaction between medical specialists at hospitals, local caregivers in the community, next of kin, and persons with SCI and PU. The RCT should identify advantages as well as challenges in the management of PU in different follow-up settings. This study aims to identify risk factors for PU after SCI, and find an effective and less time consuming treatment for the condition among different available methods for follow- up.

**Trial registration:**

www.ClinicalTrials.gov, ID: NCT02800915, last update 9 October 2017.The National Regional Ethical Committee (REC) 2014/ 684/ REK-Nord. https://helseforskning.etikkom.no/prosjekterirek/prosjektregister/prosjekt?p_document_id=469163&p_parent_id=473640&_ikbLanguageCode=n
https://app.cristin.no/projects/show.jsf?id=545284

https://www.sunnaas.no/kliniske-studier/bruk-av-telemedisin-som-virkemiddel-til-samhandling-i-poliklinisk-oppfolging-av-pasienter-med-ryggmargsskade-og-trykksar

**Electronic supplementary material:**

The online version of this article (10.1186/s13063-019-3185-y) contains supplementary material, which is available to authorized users.

## Background

In 2016, 126 persons in Norway were admitted to hospital for specialized rehabilitation after a newly acquired spinal cord injury (SCI) [1]. SCI has a huge impact on the individual, the family, and the health care system. People suffering from SCI are at particular risk of developing pressure ulcers (PUs) due to paralysis, reduced skin sensitivity, and skin exposure to moisture for extended periods of time [2]. Travelling long distances can worsen the condition or even cause new ulcers to develop [3–6]. In addition to direct treatment-related costs, PUs also have a significant impact on patient morbidity, mortality, and quality of life (QoL) [3, 7–9]. The actual number of persons with SCIs and PUs in Norway is unknown. We currently do not know the reasons that individuals develop PUs, and the best follow-up in those with SCI who develop a PU.

A narrative review concerning the use of telemedicine in the group of persons with SCI (teleSCI) for the last 20 years demonstrated many benefits, such as a high level of satisfaction, environmental favorability, and positive health-related cost-beneficial outcomes [10]. A previous feasibility study evaluated telemedicine as a possible alternative method for follow-up in the group of persons with SCI and PU [11]. Cost-benefit analysis of this feasibility study indicated that teleSCI provides savings for public health services, and that using telemedicine in other patient groups with similar problems could be beneficial [11]. This is in line with other studies demonstrating that telemedicine will reduce costs [12–14].

### Objectives and aims

This research project consists of an epidemiological analysis, called study 1, and a randomized controlled pilot trial (RCT), called study 2. In study 1, the aim is to analyze the epidemiology of persons with SCI and past or present PUs; such an approach helps to specify the extent of this complication. An important part of study 1 will be to identify risk factors for developing PUs after SCI.

The RCT aims to investigate clinical and economic aspects of follow-up by teleSCI compared to other methods. This part will assess the interaction between the specialized health care service, the users, and the caregivers using different approaches to follow-up. An important part of study 2 will be to identify challenges and advantages using different interdisciplinary health care services.

The protocol of study 2 includes questionnaires focusing on past and present PUs, risk factors for PUs and treatment applied. The practical part aims to measure the PU’s healing, evaluation of the quality of the service offered, user participation and satisfaction, as well as logistic and socioeconomic measurements. The study adds additional information regarding epidemiology and clinical courses of PUs.

The results of study 2 will have implications on, and will potentially influence future guidelines for, services innovated, interdisciplinary outpatient treatment of patients with PUs or other time-consuming follow-up conditions.

### Hypotheses

Epidemiological knowledge of persons with SCI and PUs will provide insight of this complicationCompared to other methods, PU treatment and healing will be more optimal by using teleSCI for follow-up at home measured in terms of healing, user interaction, and satisfaction

TeleSCI allows specialized hospital-based interdisciplinary teams to offer safe and effective treatment at home for persons with SCI and PUteleSCI enables specialized interdisciplinary health care workers to interact with, and empower, the primary health care workersOutpatient follow-up via teleSCI will shorten the time used for medical consultations when assessing PUOutpatient treatment via teleSCI will save money and time, compared with traditional treatment in hospital

## Methods/design

This research project consists of study 1 and study 2. The design of study 1 is a national multicenter trial, where epidemiological data of SCIs and PUs in Norway from 1 January 2004 to 1 January 2014 will be analyzed. A prevalence analysis of PUs will be performed. A statistical analysis will reveal possible risk factors for PUs after SCI.

Individuals with SCI and present PUs will be invited to participate in study 2, which is a randomized controlled pilot trial (RCT). The participants will be randomized into two groups, where one group and their local caregivers will be offered regular, interdisciplinary, outpatient follow-up by a wound team via videoconferencing, outpatient appointments at the hospital and telephone (the teleSCI group). The other group and their local caregivers will receive guidance based on existing routines, by telephone or by outpatient appointments at the hospital (the usual care group). The only difference between the follow-up in the two groups will be that the teleSCI group will be followed by regular outpatient videoconferencing consultations from the patient’s home. The interdisciplinary wound team at the SCI departments consists of a physician, a wound nurse and an occupational therapist. A plastic surgeon and an orthopedic surgeon will be supporting when needed. The local caregivers consist of local home-care nurses, and next of kin. Both groups of patients will be followed until healing of the PU, or for a maximum of 12 months (Figs. 1 and 2). A systematic and holistic evaluation of the patient will be done at baseline. A custom made journal will be used at baseline and during the follow-up period to evaluate the treatment applied. QoL and functioning will be mapped at baseline and at the end of the follow-up period. The wound size will be measured at every assessment, using validated forms and scales. Technical logistics and costs of the health care services delivered will be mapped and evaluated using custom-made forms at every assessment. In addition, a user satisfaction and participation form will be registered either when the ulcer is healed, or after a maximum of 12 months’ follow-up (Table 1). The results from the two groups will be compared with focus on ulcer healing, QoL, user participation, and satisfaction and cost-benefit. A selection of participants in the RCT study will participate in a semi-structured interview about their experiences in the follow-up (Fig. 2 and Table 1).

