**Fig. 2 Fig2:**
[figure not shown]
Standard Protocol Items: Recommended Items for Interventional Trials (SPIRIT). Template of content for the schedule of enrollment, interventions, and assessments in study 2.*

**Table 1 Tab1:** Measurement tools in studies 1 and 2

What	When	Study tool	Frequency
Study I	2017–18	Study 1 Form (EPJ)^a^	Once
		Study 2 Form (participant questionnaire)	Once
Study II	2015–19	“Calculating cost data”	Each consultation
		Interdisciplinary Wound Journal	Each consultation
		TIME^b^	Each consultation
		PWAT^c^	Each consultation
		SF-12v^d^	Baseline and 12 months/conclusion
		EQ-5D^e^	Baseline and 12 months/conclusion
		ISCI-QoL Data set^f^	Baseline and 12 months/conclusion
		SCIM III^g^	Baseline and 12 months/conclusion
	2018–2019	Observations, semi-structured interviews	Once

^a^*EPJ* electronic patient journal, ^b^*TIME* Time Infection Moisture Edge assessment scale, ^c^*PWAT* Photographic Wound Assessment Tool scale, ^d^*SF-12v* The 12-item Short Form Survey, ^e^*EQ-5D* Five Dimensions European Quality of Life scale, ^f^ISCI-QoL Data set The International Spinal Cord Injury Quality of Life Data set, ^g^*SCIM III* The Spinal Cord Injury Measurement scale, version III

The RCT part of the protocol conforms to the Consolidated Standards of Reporting Trials (CONSORT) guidelines extensions for randomized pilot and feasibility trials [15]. The study design is shown in the flow diagram in Fig. 1. The timeline for study enrollment, intervention, and assessment is described in the Standard Protocol Items: Recommendations for Interventional Trials (SPIRIT) [16] in Fig. 2. A SPIRIT Checklist [16] is included as Additional file 1. A summary of the questionnaires and forms is shown in Table 1.

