### Participants

#### Study 1

The epidemiological study includes all persons hospitalized at the three specialized SCI departments in Norway for primary rehabilitation from 1 January 2004 to 1 January 2014. All relevant persons identified will receive a questionnaire focusing on past and present PUs (Table 1). The study will run from January 2017 to May 2018 (Fig. 1).

#### Study 2

Sixty persons with SCIs and ongoing PUs, as well as their relatives and local caregivers, will be included in a RCT (Fig. 1). The participants will be randomized into two groups with 30 persons in each group. One group, their relatives and local caregivers will be offered regular, interdisciplinary, outpatient follow-up by the SCI department’s wound team at Haukeland University Hospital and at Sunnaas Rehabilitation Hospital via videoconferencing, telephone, and consultations at the outpatient wound clinic at the hospital (the teleSCI group). The other group, their relatives and local caregivers will receive guidance by the SCI department’s wound team at Haukeland University Hospital or Sunnaas Rehabilitation Hospital, based on existing routine. The follow-up will be offered by telephone and visits at the outpatient wound clinic at the hospital, based on request from the local caregivers or the patient. (the usual care group). The RCT will run from June 2015 to July 2019 (Fig. 1).

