### The teleSCI group

The participants with SCI and PU (*n* = 30) and their local caregivers will be offered interdisciplinary outpatient follow-up every second or third week, provided by the specialized SCI department’s wound team via videoconferencing. The follow-up will consist of teleSCI appointments, visits to the SCI outpatient wound clinic at the hospital and telephone consultations. The Template for Intervention Description and Replication (TIDieR) [31] Checklist and Guide (Table 2) has been used to record and describe the intervention by teleSCI. This will secure treatment fidelity, replication for future trials, and transparency of reporting the results.

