### The usual care group

The participants with SCIs and PUs (*n* = 30) and their local caregivers will receive guidance based on existing routines provided by the specialized SCI department’s wound team. Telephone contact and appointments at the SCI outpatient wound clinic will be based on initiative taken by the local health care service/patient/next of kin. As usual, as care services vary in type and frequency, the follow-up provided for each participant will depend on the local resources available.

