### Statistical analysis

Data from the end of the study will be analyzed using chi-square tests for categorical data and *t* tests for continuous data. Regression analyses (linear and logistic) will be performed to make any necessary adjustments for baseline differences. In addition, we will also analyze developments over time in the two groups, using the mixed-models analysis.

Mean QoL scores with corresponding 95% confidence interval will be estimated in each of the two treatment groups, and the groups will then be compared using *t* tests and mixed-models analysis. A cost-benefit analysis will be carried out to assess the cost of outpatient treatment via telemedicine, compared with outpatient treatment at the hospital.

The reduction (in percentage) of PU size is calculated with corresponding 95% confidence interval for each of the two treatment groups. The groups will be compared with regard to percentage reduction in ulcer size, using *t* tests and mixed models. All quantitative statistical analyses will be performed using the SPSS and STATA statistical software package. Computer Assisted Qualitative Data Analysis (CAQDAs) will be used in the qualitative analysis.

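### Wound measurement follows arm-specific contacts, so time to heal can favour teleSCI if usual-care contacts are sparser and healing is dated when it is seen

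*Protocol article*

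**What the plan says.** Two statements fix when the ulcer is observed in study 2. Methods/design: "The wound size will be measured at every assessment, using validated forms and scales". Table 1 gives the frequency of the wound journal, TIME and PWAT as "Each consultation". Only the quality-of-life scales and SCIM III are tied to baseline and to 12 months or conclusion.

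The frequency of contacts differs by design. Participants in teleSCI "will be offered interdisciplinary outpatient follow-up every second or third week", and Table 2 gives the same frequency. For usual care, "Telephone contact and appointments at the SCI outpatient wound clinic will be based on initiative taken by the local health care service/patient/next of kin". The Participants section likewise describes this follow-up, by telephone and clinic visits, as "based on request from the local caregivers or the patient". No interval is given, and the usual care section says provision varies with local resources.

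Primary endpoints names the percentage of wound size healed and the time to heal. Time to heal is counted in days, with the amount of healing at 12 months used otherwise. The source of the healing date is not stated. Statistical analysis lists chi-square tests, t tests and regression, and adds that "we will also analyze developments over time in the two groups, using the mixed-models analysis".

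**The concern.** The randomised intervention also determines how often a primary endpoint is observed. An ulcer that closes between contacts is known to have closed only at the next one, unless someone else dates it. If the wait is longer in usual care, the same biological healing is recorded later there. The t test on days to healing would read that delay as a treatment effect, in the direction the trial hypothesises.

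The mixed model has a related problem. teleSCI contributes many size measurements at roughly even spacing. Usual care contributes a number that depends on who asks for help. Some of those contacts are telephone calls, for which the text does not say how a wound would be measured. If requests tend to follow deterioration, measurement times depend on wound status, and the usual-care trajectory over-represents bad moments.

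Blinded rating (Blinding section) addresses who judges the wound, not when it is seen. None of the listed analyses corrects for observation that differs by arm.

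**Working it through.** **The plan's own figures.** The article gives no figure for detection delay. Its sample size gives the scale: with a standardized difference of 0.8, 80% power and an assumed two-sided 5% level, n = 2(1.960 + 0.842)² / 0.8² = 24.5, so 25 per group as stated, raised to 30 for drop-out.

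**Inputs from the article.** teleSCI interval 14-21 days, midpoint 17.5; 30 per arm; follow-up capped at 365 days.

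**Assumptions.** Usual-care interval 28, 56 or 84 days; each interval varies uniformly by ±50% in both arms; 50-90% truly healed by 12 months, with the same constant healing rate in both arms; healing dated at the next contact, with a close-out look at day 365.

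**Mean delay.** For contacts with mean interval g and squared coefficient of variation CV², the mean wait from closure to the next contact is (g/2)(1 + CV²). A uniform spread of ±50% gives CV² = 1/12, so the wait is g × 13/24.

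- teleSCI: 17.5 × 13/24 = 9.5 days.
- Usual care: 28, 56 and 84 × 13/24 = 15.2, 30.3 and 45.5 days.

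Only healed participants carry the delay, so the expected difference in capped days to healing is roughly the excess delay times the proportion healed. The last two columns come from simulation under equal healing, using the t test that the article names for continuous data.

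| Usual-care interval (assumed) | Excess delay | Excess × 0.5 to 0.9 | Simulated difference | False positives favouring teleSCI (nominal 2.5%) |
|---|---|---|---|---|
| 4 weeks | 5.7 days | 2.8-5.1 | about 2-5 days | about 3% |
| 8 weeks | 20.9 days | 10.4-18.8 | about 10-19 days | about 5-10% |
| 12 weeks | 36.0 days | 18.0-32.4 | about 17-35 days | about 8-24% |

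The hand calculation and the simulation agree.

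**Sensitivity.** These runs assumed a median healing time of 90 or 180 days.

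- Equal regular intervals of 17.5 days in both arms: the two-sided error is 0.050-0.052, so the bias vanishes.
- Usual-care contacts random in time (CV² = 1): the delay equals the mean interval. At a mean of 56 days, two-sided error is about 0.17-0.33, nearly all favouring teleSCI.
- Regular usual-care contacts: the spurious standardized difference is 0.12-0.19 at 56 days and 0.21-0.35 at 84 days, against the planned 0.8.

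**The case against.** The strongest reply is that the dating mechanism is not in the text. The article does not say healing is dated at the first contact after closure. The Intervention section carries the principle of a few dedicated home-care nurses and a common description of ulcer status into both groups, so local observers who could date closure exist in both arms. Both arms are followed to healing, and the satisfaction form is completed when the ulcer has healed, so healing should prompt a study contact in usual care too. Fig. 2, the assessment schedule, is not available and could contain common time points. If closure reported by telephone were accepted in usual care, it could even be dated early there.

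Much of this stands, and it makes both the direction and the size conditional. It does not remove the point. The text gives no rule by which a nurse's date becomes the endpoint, and the measurement rule it does state depends on arm. This is therefore more than detail left to a fuller document.

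A reader might also infer that cost data and adverse events are biased in the same way. The article does not support that. Fewer consultations genuinely cost less, so recording costs per contact is not in itself unequal capture. Secondary endpoints also asks for medication and bandages at each treatment session, at home as well as in hospital. Nothing in the article puts a figure on over-recording of adverse events in teleSCI.

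**Conclusion.** The point holds in conditional form and should be fixed; confidence is medium. As written, the plan lets the frequency of wound observation differ by arm while counting days to healing as a primary endpoint. If usual-care contacts are sparser than every two to three weeks and healing is dated when seen, time to heal is biased towards teleSCI. The effect is negligible to small at 4 weeks and material at 8-12 weeks, particularly when most ulcers heal. All usual-care intervals and healing proportions are assumed, because the article gives none.

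Two stronger readings should be resisted. One is that healing is certain to be detected earlier in teleSCI; that depends on a contact frequency and a dating rule that the text does not give. The other is that both healing endpoints are equally compromised. Percentage reduction at 12 months is much less affected, since a healed ulcer counts as 100% whenever it is detected. The exposure lies in time to heal and in the longitudinal size analysis.

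**What to change.** 1. For every participant in both arms, record the last date the ulcer was seen unhealed and the first date it was seen healed, using the home-care nurse's or wound journal's date where there is one. Analyse time to heal as interval-censored between these dates.
2. For participants still in follow-up, add wound-size measurements on calendar dates common to both arms, taken by the existing home-care nurse independently of wound-team contacts. Use them in a sensitivity analysis of the mixed model and keep all existing data in the main model. Restricting the model to the new dates would discard information: Trial status reports about 50 randomised and nearly 40% of them finished, or about 0.4 × 50 = 20 people who cannot supply such measurements.

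The care schedules in both arms stay as they are.

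The cost is some nurse time and a minor amendment. Data entry had not begun when Trial status was written, so the two dates could be built into it. One limitation should be stated in the report: standard interval-censored methods assume that contact times do not depend on the wound. If usual-care contacts are prompted by its condition, the bias is reduced but not fully removed.
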